#### Exclusion criteria

2.4.2

Participants will not be eligible if they meet one or more of the following criteria:

1.A previous history of nose-related or allergy-related disease and treatment, including any of the following:A.Congenital deviated nasal septum, nasal polyps, acute or chronic sinusitis, asthma symptomsB.Use of topical decongestants or cromolyn sodium within the previous 3 daysC.Use of antihistamines or anticholinergics within the previous weekD.Use of intranasal or oral steroids within the previous 2 weeksE.Use of leukotriene receptor antagonists within the previous 4 weeksF.Use of Korean medicine treatment (acupuncture, moxibustion, herbal medicine, cupping, etc) for the treatment of AR within the previous monthG.Receipt of immunotherapy within the previous 5 years2.Presence of serious medical conditions that could interfere with clinical trial participation, including any of the following:A.Hypertension (systolic blood pressure greater than 160 mm Hg or diastolic blood pressure greater than 100 mm Hg)B.Diabetes mellitus (fasting blood glucose greater than 126 mg/dL)C.Renal dysfunction (serum creatinine level more than twice the normal range)D.Liver function abnormality (alanine aminotransferase or aspartate aminotransferase levels that are more than twice the upper limit of the normal range)E.Serious hyperlipidemia, anemia, active tuberculosis, thyroid disease, or other serious inflammatory or systemic diseaseF.Past or present history of malignant tumors3.Pregnancy or breast-feeding4.Other; ineligible for participation as judged by the investigator:A.Those who cannot use mobile applications to record symptoms of AR daily.

After voluntary consent to the study, potential participants will be screened using MAST at the first visit to determine if the rhinitis is allergic. In the MAST, the amount of IgE present in the serum is measured to determine the cause of 92 kinds of respiratory and food allergies and to determine the severity of the allergic reaction.^[24]^ To rule out the possibility of suppression of allergic reaction, drugs containing antihistamines and steroids will be stopped a week before the test. At any time during the clinical trial, the participant may voluntarily withdraw from the clinical trial or can be dropped at the researcher's discretion.

### Intervention

2.5

Participants will receive SCRT or cetirizine for 2 weeks. Participants in the intervention group will receive SCRT. They will take a packet of the medicine (3.0 g) with water twice a day before breakfast and dinner. Participants in the control group will receive cetirizine. They will take 1 tablet (10.0 mg) before bedtime. The dosage regimen is determined according to MFDS approvals.^[16]^

SCRT (Kracie sho-seiryu-to, K-02) is light brown fine granule with some sour and sweet taste. SCRT will be supplied by Kracie (Kracie Pharmaceutical, Ltd. Tokyo, Japan). A 6.0 g sample of SCRT contains 5.2 g of a dried extract which consists of eight medicinal herbs, *Pinellia tuber* 6.0 g, *Schisandra fruit* 3.0 g, processed ginger 3.0 g, cinnamon bark 3.0 g, *Glycyrrhiza* 3.0 g, *Ephedra herb* 3.0 g, *Asiasarum* root 3.0 g, and peony root 3.0 g. Quality control and quality assurance regarding the identification of products as well as quality and safety testing will be conducted by the manufacturer, which is certified for good manufacturing practices of herbal medicine granules by the Korean MFDS. In qualitative testing, isopropanol, ephedrine, glycyrrhizin, and paeoniflorin are determined in the laboratory of Kracie (Kracie Pharmaceutical, Ltd. Tokyo, Japan) using thin layer chromatography analysis.

Cetirizine is an over-the-counter drug in South Korea. We will record the drugs taken by each participant at every visit to confirm adherence to the protocol. Also, participants will be requested to notify us of any change to their medication/supplement regimen. Additional acupuncture treatments, herbal prescriptions, or therapeutic interventions by other clinicians will not be allowed during the treatment period.

### Outcome measures

2.6

#### Primary outcome

2.6.1

The primary outcome is the change in total nasal symptom score (TNSS). TNSS will be recorded in participants’ diaries every day before bedtime using a mobile application. A 4-point severity scale (no symptoms, 0; mild, 1; moderate, 2; and severe, 3) will be used.^[25]^ Using 4 weeks of TNSS scores, we will analyze the differences in the effects of SCRT and cetirizine, and the duration of the effects of each medication.

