**Methods and analysis::**

This is a randomized, open-label, cetirizine-controlled clinical trial. A total of 30 AR patients who have signed informed consent forms will be recruited and randomly assigned to SCRT or cetirizine groups at a 1:1 ratio. The participants will visit the clinical research center every week and receive SCRT granules or cetirizine tablets. SCRT will be taken twice daily, cetirizine will be taken once daily, and treatment medication will be taken for 2 weeks. Data will be collected at baseline, at week 2, and at week 4 after random allocation. The primary outcome will be the mean change in the total nasal symptom score from baseline to week 2. Secondary outcome measures will include the mini Rhinoconjunctivitis Quality of Life Questionnaire and total serum immunoglobulin E. To assess the safety of SCRT, a liver and renal function test will be conducted before and after treatment, and the participants will be asked about any occurrence of adverse events at every visit. The recruitment rate, completion rate, and medication adherence will also be calculated to assess feasibility.

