### Trial design and setting

2.2

This is a randomized two-parallel-arm open-label cetirizine-controlled comparative effectiveness study. This study will be conducted at Woosuk Korean Medicine Medical Center, Jeonju, Republic of Korea. The study has 2 arms: the SCRT treatment group and the cetirizine control group. A total of 30 participants will be recruited for this trial. Cetirizine will be used as an active control to compare the effectiveness of SCRT on AR patients whose symptoms are not controlled by conventional medication. The total study period will be 5 weeks. It consists of a week run-in period after screening, 2 weeks of medication, and 2 weeks of follow-up after medication is stopped.

The detailed design is summarized in Fig. 1 and Table 1. The study protocol (version 1.3) follows the Standard Protocol Items: Recommendations for Interventional Trials (SPIRIT) guidelines (see Additional File 1).

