### Blinding

2.9

To avoid selection bias, the randomization of serial numbers will be managed using sealed envelopes and a locked cabinet. Investigators will open a sealed envelope when a participant is enrolled. The experimental drug in this trial is an herbal medicine that is provided in granules, while the control medication is a drug that comes in tablets. Because patient blinding is not possible, the trial is designed as open label. Although the subjective symptoms of subjects is the main outcome, total serum IgE and Nasal Endoscopy Index will also be examined. The Nasal Endoscopy Index test will be conducted by an investigator who has not been informed about the random assignment and medication and does not know to which group each subject is assigned. This process is intended to reduce the possibility of bias by the evaluators.

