### Statistical analysis

2.11

An independent statistician who is blinded to the randomized allocation of participants will carry out the statistical analysis. Measured variables will be assessed using the full analysis set based on intention-to-treat principles, including all randomized participants who completing the trial without violating any of the exclusion criteria and for whom a complete set of data is available. The per-protocol analysis set will be used for the sensitivity analysis.

The demographic characteristics and baseline data of both groups will be summarized by means and standard deviations for the continuous variables, and frequencies and percentages will be presented for categorical variables. Baseline differences between groups will be assessed using independent *t* tests or Mann–Whitney *U* tests for continuous variables, and the chi-squared test or Fisher exact test for categorical variables. Differences in the primary and secondary outcomes will be analyzed using one-sided independent *t* tests. To demonstrate noninferiority, we will check whether the lower limit of the 2-sided 95% CI of the difference of the primary outcome between the 2 groups is greater than the noninferiority margin. The analysis will be presented as a difference with an associated 95% CI. To determine whether statistically significant differences exist between the groups, differences in the primary and secondary outcomes will be analyzed using a mixed effects model for repeated measurement. Subgroup analyses will also be conducted to investigate the difference in treatment effect according to the type of cold–heat pattern identification questionnaire, each symptoms of AR, and the results of Nasal Endoscopy Index. The level of significance will be set at 0.05 (2-tailed), and all analyses will be performed using SAS (V.9.4; SAS Institute).

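### Section 2.6.1 promises a duration of effect for each drug, but two active open-label arms identify only the difference between them in weeks 3 and 4

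*Protocol article*

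**What the plan says.** Section 2.6.1 of the Protocol article sets two targets for the four weeks of daily TNSS. One is the difference between SCRT and cetirizine. The other is "the duration of the effects of each medication", which is worded per drug.

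Section 2.2 fixes the design: "The study has 2 arms: the SCRT treatment group and the cetirizine control group". Cetirizine is described there as an active control, and no placebo or untreated group appears. The timetable after a one-week run-in is "2 weeks of medication, and 2 weeks of follow-up after medication is stopped".

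Section 2.9 adds: "Because patient blinding is not possible, the trial is designed as open label". TNSS is recorded by the participants themselves.

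The Abstract places the primary endpoint at the end of treatment: "The primary outcome will be the mean change in the total nasal symptom score from baseline to week 2". The only longitudinal method named, in Section 2.11, is between-group: "differences in the primary and secondary outcomes will be analyzed using a mixed effects model for repeated measurement".

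**The concern.** Because the diaries run two weeks beyond the last dose, the duration of each drug's effect includes how long it lasts after stopping. Within one arm, the evidence for persistence would be a TNSS that stays low in weeks 3 and 4. That pattern has several explanations besides a lasting drug effect:

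- the natural course of the rhinitis;
- a change in allergen exposure;
- regression to the mean in people who enrol while symptomatic;
- reporting by participants who know what they took.

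Without an arm that shows what happens off drug, the data cannot choose among them.

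At stake is the conclusion drawn for the next trial. The Introduction lists loss of effect after stopping as a drawback of conventional drugs, and the Discussion says that the findings should support a full-scale trial. A low off-drug score in the SCRT arm could be reported as a lasting effect of SCRT when the design does not support that statement.

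**Working it through.** **Plan's own figure.** The plan states no figure for duration of effect, so there is none to reproduce. Its one sample-size calculation (Section 2.10) does reproduce: 12 / (1 − 0.20) = 15 per arm, 30 in total. It has no bearing on this point.

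**Inputs.** Two active arms, two weeks on drug and two weeks off (Section 2.2); daily TNSS over four weeks (Section 2.6.1), that is 4 weekly means or 28 daily means per arm.

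**Step 1: what two active arms can identify.** Write the mean TNSS of arm k at time t as

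m_k(t) = b + n(t) + e_k(t),

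where b is the common baseline (taken as known), n(t) is everything other than drug that moves both arms alike, and e_k(t) is the effect of drug k. With T time points there are 2T observed means and 3T unknowns: n(t), e_SCRT(t) and e_cet(t).

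| Time scale | Unknowns | Rank, two active arms | Rank with a hypothetical untreated arm |
|---|---|---|---|
| Weekly, T = 4 | 12 | 8 | 12 |
| Daily, T = 28 | 84 | 56 | 84 |

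Adding any constant to n(t) and subtracting it from both drug effects leaves every observed mean unchanged. So e_SCRT at week 4 is not estimable, and neither is e_cet. The difference is estimable, because b and n(t) cancel:

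m_SCRT(t) − m_cet(t) = e_SCRT(t) − e_cet(t).

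More frequent diary entries do not help; the shortfall is the same on the daily scale.

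**Step 2: what this means for a duration (all figures assumed; the documents give none).** Suppose the SCRT arm changes by −3 points at week 2 and −2 at week 4, and the non-drug change is linear, so that its week-2 value is half its week-4 value n4. Then:

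remaining drug effect at week 4 = −2 − n4

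retained share of the week-2 effect = (−2 − n4) / (−3 − n4/2)

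| n4 | Remaining effect | Retained share |
|---|---|---|
| 0 | −2.0 | −2 / −3 = 67% |
| −0.5 | −1.5 | −1.5 / −2.75 = 55% |
| −1.0 | −1.0 | −1 / −2.5 = 40% |
| −1.5 | −0.5 | −0.5 / −2.25 = 22% |
| −2.0 | 0 | 0 / −2 = 0% |

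The same observed course fits an effect that largely persists and one that has gone.

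**Step 3: the between-arm difference is not a duration either.** A difference of 0 at week 4 follows if both effects are 0 and equally if both are −1. The contrast shows whether one drug leaves patients better off than the other after stopping, not how long either lasts.

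**Step 4: is an off-drug reference given elsewhere?**

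- The run-in week (Section 2.2) is not named as a reference for natural course. Carrying a one-week pre-treatment trend forward four weeks would itself be an assumption.
- The Introduction says in general that conventional drugs lose their effect once stopped. Using post-treatment cetirizine as the reference on that basis would assume the cetirizine duration that the plan sets out to estimate.
- Section 2.11 gives no within-arm estimator and does not define duration.

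**The case against.** The strongest reply is that the sentence in Section 2.6.1 is loose and may only mean comparing the two drugs, including how the comparison evolves. Every outcome test in Section 2.11 compares groups, and the planned mixed model could already give the weeks 3 and 4 contrast. The words after stopping are also not in Section 2.6.1; they are inferred from the timetable in Section 2.2. This is a fair account of the methods, but it does not remove the per-drug wording, which stands beside the comparative target as a second one. Nor is it a detail for an analysis plan to settle, since no analysis can recover a per-drug effect here without an outside assumption about the off-drug course.

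It is also true that daily diaries can show symptoms returning after the last dose, which would suggest that an effect had ended. That stands. The uninterpretable case is the sustained low score, which is the one that would be read as persistence.

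Four stronger readings are tempting, and the documents do not support them:

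- **That scores would fall anyway, by a known amount.** Section 2.4.1 sets no minimum TNSS, and its criteria select long-standing disease rather than a momentary peak. Allergen exposure could raise scores as well as lower them. Regression to the mean is one candidate among several, and nothing in the documents gives its size.
- **That the article claims SCRT effects persist.** The Introduction criticises conventional drugs on this ground but makes no such claim for SCRT.
- **That a duration will be claimed in a selected group, such as early responders.** No such analysis is proposed.
- **That the main comparison is undermined.** It is a between-group contrast at week 2, which this point does not touch.

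**Conclusion.** The point holds and is minor. The design cannot deliver a duration of effect for either drug alone; it can deliver the SCRT–cetirizine difference in weeks 3 and 4. The size of the possible error cannot be stated from the documents. The 67% to 0% range shows non-identifiability under assumed scores and is not an estimate for this trial.

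The conclusion rests on three readings: that the four weeks are those after randomization, that duration includes the two weeks off drug, and that no off-drug reference exists beyond what the text describes. Randomization balances natural course, exposure and regression to the mean between the arms. It does not remove differences in reporting that may arise because participants know their treatment, so even the between-arm contrast needs that caveat.

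The week-2 primary comparison and the feasibility measures in Section 2.7 are unaffected.

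**What to change.** In Section 2.6.1, replace the per-drug duration wording with: *the between-group difference in mean TNSS during weeks 3 and 4 after stopping*. Then specify three things:

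1. The contrast is secondary and separate from the week-2 comparison. It is estimated with baseline TNSS as covariate in all randomized participants, for example from the mixed model already planned in Section 2.11. The population should be stated, because the full analysis set there is described as limited to participants who finish with complete data, and that restriction would weaken the protection of randomization.
2. Within-arm time courses, including any return of symptoms after the last dose, are presented as descriptive only.
3. No duration of effect is claimed for either drug on its own.

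The cost is a change of wording, one pre-specified contrast and a narrower claim. The diary data are already planned, so no new arm, visit or measurement is needed.

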#### Secondary outcomes

2.6.2

Secondary outcomes include the mini Rhinoconjunctivitis Quality of Life Questionnaire (RQLQ) and total serum IgE, which will be measured 3 times in total, at screening and 2 and 4 weeks after randomization. The mini-RQLQ is an abbreviated form of the RQLQ, and consists of 14 questions about activities, behavioral problems, nose symptoms, eye symptoms, and other symptoms related to AR. Each item produces a score from 0 to 6 according to the severity of the symptoms.^[26,27]^

To evaluate the effects of SCRT on allergic and inflammatory reactions, we will examine differential white blood cell counts (neutrophil, eosinophil, basophil, monocyte, and lymphocyte) and conduct total serum IgE tests at 2 and 4 weeks after randomization.

To search for the more precise indication of using SCRT, we will use the Cold–Heat Pattern Identification Questionnaire and Nasal Endoscopy Index. The Cold–Heat Pattern Identification Questionnaire is used to distinguish between cold and heat, which is a characteristic of patients from a Korean traditional medicine perspective. The questionnaire consists of 15 symptom-based items, including 8 items related to cold and 7 items related to heat. According to the results of this questionnaire, a patient could be classified as Cold, Heat, neither Cold nor Heat and Cold–Heat complex.^[28]^ The Nasal Endoscopy Index will be used for supplementary evaluation of subjective symptoms of TNSS at the time of randomization and 1, 2, and 4 weeks after randomization. The instrument used is the KAZAMA ENT treatment unit (KAU-3000, HARMONY, ENT Co., Ltd., Incheon, Korea). The efficacy is assessed by scoring the status of the nasal cavity according to an assessment scale developed by Yun et al. It consists of 4 categories for the evaluation of color, dryness/dampness, nasal discharge, and atrophy/edema of the lower nasal turbinates, using a 3-point severity scale scored from normal (0), mild (1), to severe (2).^[29]^

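### The only pre-treatment mini-RQLQ is taken at screening, one week before randomization, so each change score includes an untreated week (minor; no expected bias between arms)

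*Protocol article*

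**What the plan says.** Section 2.6.2 (Secondary outcomes) gives one schedule for both the mini-RQLQ and total serum IgE, "which will be measured 3 times in total, at screening and 2 and 4 weeks after randomization". The count of three leaves no room for a further mini-RQLQ at randomization. (Table 1, the visit schedule, was not legible in the text to hand.)

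Section 2.2 (Trial design and setting) sets out the calendar: "The total study period will be 5 weeks", and "It consists of a week run-in period after screening, 2 weeks of medication, and 2 weeks of follow-up after medication is stopped".

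The Nasal Endoscopy Index, also in section 2.6.2, has its first score at randomization. It is taken "at the time of randomization and 1, 2, and 4 weeks after randomization".

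For the TNSS, the abstract defines the primary outcome: "The primary outcome will be the mean change in the total nasal symptom score from baseline to week 2". Section 2.6.1 adds that "TNSS will be recorded in participants’ diaries every day before bedtime using a mobile application" and "Using 4 weeks of TNSS scores, we will analyze the differences in the effects of SCRT and cetirizine". No sentence dates the TNSS baseline.

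The abstract summarizes the visits as "Data will be collected at baseline, at week 2, and at week 4 after random allocation", without saying whether baseline means screening or randomization.

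**The concern.** A change score is easiest to read when its baseline is taken just before treatment starts. Here the quality-of-life baseline comes from the screening visit, and a full untreated week separates it from the first dose. Two secondary outcomes described in the same section therefore have different starting points, and the article gives no reason.

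Two things are at stake. First, if quality of life shifts during the run-in for any reason, the shift is included in the change reported for each arm, and a reader may take it for a drug effect. Second, a baseline further from follow-up usually predicts the follow-up value less well, which costs precision in a trial of 15 patients per group. The trial is meant to prepare a full-scale one, so the schedule, and any standard deviation of change estimated from it, may be carried forward.

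**Working it through.** **Calendar (section 2.2).** Run-in 1 week + medication 2 weeks + follow-up 2 weeks = 5 weeks, which reproduces the stated study period. Weeks 2 and 4 after randomization then fall at the end of medication and the end of follow-up. This places randomization at the end of the run-in, 1 week after screening.

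**Length of each change interval.**

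| Outcome | Baseline | To week 2 | To week 4 |
|---|---|---|---|
| mini-RQLQ | screening | 1 + 2 = 3 weeks | 1 + 4 = 5 weeks |
| Nasal Endoscopy Index | randomization | 2 weeks | 4 weeks |

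The untreated run-in is 1/3 = 33% of the mini-RQLQ interval to week 2 and 1/5 = 20% of the interval to week 4.

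**Effect on the means.** Let d be the mean shift during the run-in, and let E1 and E2 be the mean changes from randomization to week 2 in the two arms. The expected change from screening is d + E1 in one arm and d + E2 in the other, because allocation comes after the run-in and d has the same expectation in both. The between-arm difference is (d + E1) − (d + E2) = E1 − E2. So d enters each arm's own change in full and drops out of the comparison.

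**Effect on precision.** The document gives no correlations. As an assumption, take r = 0.6 between the randomization and week-2 values, r = 0.5 between the screening and week-2 values, and equal variance at each time.

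- Raw change scores have variance 2(1 − r)SD². This is 2 × 0.4 = 0.8 SD² from randomization and 2 × 0.5 = 1.0 SD² from screening. The ratio is 1.25, and √1.25 = 1.12, so intervals are about 12% wider.
- With baseline as a covariate, the residual variance is (1 − r²)SD². This is 1 − 0.36 = 0.64 SD² against 1 − 0.25 = 0.75 SD². The ratio is 1.17, and √1.17 = 1.08, so intervals are about 8% wider.
- If only post-treatment scores are compared, the baseline is not used and nothing is lost.

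**Range under another assumption.** Suppose the correlation decays geometrically at ρ per week, so r = ρ² from randomization and r = ρ³ from screening to week 2. The ratios of standard deviations (screening over randomization) are:

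| ρ per week | Raw change | Baseline as covariate |
|---|---|---|
| 0.7 | 1.146/1.010 = 1.13 | 0.939/0.872 = 1.08 |
| 0.8 | 0.988/0.849 = 1.16 | 0.859/0.768 = 1.12 |
| 0.9 | 0.736/0.616 = 1.19 | 0.685/0.586 = 1.17 |
| 0.95 | 0.534/0.442 = 1.21 | 0.515/0.431 = 1.20 |

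These figures show a plausible order of size. They are not estimates for this trial.

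**The case against.** The strongest reply is that a screening baseline is a legitimate choice and harms no planned comparison. Section 2.11 (Statistical analysis) describes only between-group analyses of the outcomes: independent t tests, a difference with its interval, and a mixed model. A reader might infer that the untreated week biases the comparison of SCRT with cetirizine. The document does not support that, because screening precedes allocation in both arms. No within-arm test of the mini-RQLQ is stated either, so the effect on means is confined to descriptive changes.

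A reader might also infer that regression to the mean or drug withdrawal is bound to move scores during the run-in. Section 2.4.1 sets no threshold on the mini-RQLQ or TNSS at screening; entry rests on the type, frequency and duration of symptoms and on a positive MAST. Section 2.4.2 requires antihistamines and steroids to be stopped a week before the MAST, which is done at the first visit, so washout falls largely before screening. Drift in the run-in is possible, but neither its presence nor its direction can be shown from the text.

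A third tempting inference is a mismatch with the primary outcome. Four weeks of TNSS scores equals medication plus follow-up, which points towards a baseline at randomization, but the article does not date that baseline. Only the mismatch with endoscopy is explicit.

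Finally, the precision loss rests on assumed correlations and on how the baseline is used, which section 2.11 does not settle for the mini-RQLQ.

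All four objections limit the point. What stands is the schedule itself: one pre-treatment mini-RQLQ, a week old at randomization, although endoscopy is already scored at the randomization visit.

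**Conclusion.** The point holds as a minor design weakness. By the article's own calendar, the mini-RQLQ change to week 2 covers 3 weeks and the change to week 4 covers 5 weeks, with 1 untreated week in each. Two consequences follow: run-in drift, if there is any, is mixed into each arm's descriptive change, and some precision is probably lost. Under correlations of 0.6 and 0.5 the loss is about 12% in interval width for raw change, about 8% with baseline adjustment and nil without use of the baseline. Under the decay assumption it runs from about 8% to 21% whenever the baseline is used. All these percentages depend on correlations that the document does not give. The severity is low: the matter concerns one secondary outcome in a feasibility trial whose sample size was not set by power.

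**What to change.** Split the sentence in section 2.6.2 that times the mini-RQLQ and total serum IgE together.

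- **mini-RQLQ:** completed at the randomization visit, before the envelope is opened, and at 2 and 4 weeks after randomization. The randomization value is the baseline. Completion before the envelope is opened matters because the trial is open label and knowledge of the allocation could colour the answers.
- **Total serum IgE:** timing stated in its own sentence. It stays at screening and at weeks 2 and 4, with the first value labelled as the screening value. Changing the shared sentence without splitting it would move IgE as well.

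Table 1 and the abstract's reference to baseline should be brought into line. The cost is a change of wording and the move of one 14-item questionnaire to a visit already held for nasal endoscopy. No visit, procedure or patient is added.
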